**Methods:**

The trial is a prospective randomized controlled study with 2 × 2 balanced factorial design. Patients eligible for the study will be randomized to 4 groups: (I) Laparoscopic surgery with fast track perioperative treatment and Xelox chemotherapy; (II) Open surgery with fast track perioperative treatment and Xelox chemotherapy; (III) Laparoscopic surgery with conventional perioperative treatment and mFolfox6 chemotherapy; (IV) Open surgery with conventional perioperative treatment and mFolfox6 chemotherapy. The primary endpoint of this study is the hospital stays. The secondary endpoints are the quality of life, chemotherapy related adverse events, surgical complications and hospitalization costs. Totally, 340 patients will be enrolled with 85 patients in each group.

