## Methods/Design

### Study objectives

The general objective of this FTMDT trial is to assess, synthesize and discuss the feasibility of "Fast Track Multi-Discipline Treatment" model in treatment of colorectal cancer. It can be divided into 2 questions: 1. Is it safe and effective to combine Xelox chemotherapy with laparoscopy and fast-track perioperative treatment? 2. Is laparoscopy an essential component of FTMDT and how important a role does it play?

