### Study design

This FTMDT-trial is an open randomized prospective and controlled study with 2 × 2 balanced factorial design. Patients eligible for the criteria will be randomized into four study groups (1:1:1:1) according to the randomized figures generated by the SPSS 16.0, after the patients signing the informed consents: (I) Laparoscopic surgery with fast track perioperative treatment and Xelox chemotherapy; (II) Open surgery with fast track perioperative treatment and Xelox chemotherapy; (III) Laparoscopic surgery with conventional perioperative treatment and mFolfox6 chemotherapy; (IV) Open surgery with conventional perioperative treatment and mFolfox6 chemotherapy.

Chinese medical insurance system ensures that, hospitalization is suitable for payment and also for patients' interest. All patients in this study will receive hospitalized chemotherapy in each cycle.

This trial has the independent "third-party" for developing the randomization.

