### Primary and secondary endpoint measures

The primary outcome measure of this FTMDT-trial is the hospital stays, which is the overall hospitalization stay during treatment including both the hospital stay for the surgery and adjuvant chemotherapy.

We define the postoperative discharge day for the patients in the trial when they meet all of the discharge criteria, 1. Good pain control: NSR (Numeric Rating Scale) ≤ 3. 2. Tolerance of solid food, no need of intravenous fluid infusion. 3. Independent activities of daily living (ADL) to preoperative care level at least [18,19].

Secondary outcome measures are as follows, 1. Quality of life according to EORTC (European Organization for Research and Treatment) QLQ-C30 and QLQ-CR38 questionnaires, with the checkpoint frame, preoperation, 1 week post operation, 3-months post surgery and 6-months post surgery. 2. Chemotherapy related adverse events according to NCI CTCAE (Common Terminology Criteria for Adverse Events) Version3.0. 3. Surgical complications mainly include injury of the ureters, intraoperative transfusion, infection of incision, anastomotic leakage and readmission. 4. Hospitalization costs are calculated from the first day in hospital to the last day that adjuvant chemotherapy is finished.

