- Intravenous fluid infusion	- Stop intravenous high energy fluid infusion after dosage of Enteral Nutritional Emulsion Supportan ≥ 600 ml or Enteral Nutritional Emulsion Fresubin Diabetes ≥ 500 ml	- Intravenous high energy fluid infusion on daily basis and continuing until adequate oral intake
	
	- No intravenous High-energy Nutrient Fluid after 72 h post-surgery	
	
	- Restricting and avoiding excessive intravenous fluid infusion, keeping body weight as pre-surgery	

- Energy	- Keep the total energy intake (both diet and intravenous fluid infusion) 25-30 kcal/kg/day	- Keep the total energy intake (both diet and intravenous fluid infusion) 25-30 kcal/kg/day

- Nasogastric tube and urethral catheter	-Remove nasogastric tube as soon as the end of operation	- Remove nasogastric tube after 1st flatus postoperation

	- Remove urethral catheter within 24-48 h after operation	-Remove urethral catheter when 1st time meet: patient have the feeling of automatic micturition and ≧200 ml after valving-on urethral catheter

- Ambulation	- Forced ambulation within 24 h post-surgery, no time restriction	- No ambulation scheme
	
	- Ambulation time ≥ 1 h per day, and increasing day by day	
	
	- Patients walking to weight themselves every day	

Adjuvant		

chemotherapy	- Xelox	- mFolfox6
	
	- repeat every 3 weeks for 8 cycles	- repeat every 2 weeks for 12 cycles
	
	- Regimen	- Regimen
	
	Oxaliplatin 130 mg/m2 day 1, Capecitabine (Xeloda™) 850-1,000 mg/m2 twice daily for 14 days -	Oxaliplatin (Eloxatin^TM^) 85 mg/m2 IV over 2 hours, day .1 Leucovorin (Tongao™) 400 mg/m2 IV over 2 hours, day 1. 5-FU (Jinyao™) 400 mg/m2 IV bolus on day 1, then 1,200 mg/m2/day × 2 days (total 2,400 mg/m2 over 46-48 hours) continuous infusion
	
	- No peripherally inserted central catheter (PICC)	- Peripherally inserted central catheter and care of PICC in outpatient clinic every week
	
	- Hospitalization no more than 24 h each cycle	- Hospitalization for 3 days each cycle

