The NO16968/XELOXA study discovered that the Xelox chemotherapy used as an adjuvant chemotherapy for colorectal cancer become possible now, as it has a manageable tolerability profile in adjuvant setting [17]. In each cycle of Xelox chemotherapy, there is only 1 day hospital stay for intravenous Oxaliplatin and the Capecitabine intake from 1st to14th day can be done in home. And in mFolfox6 chemotherapy, each cycle needs 3 days hospital stay in China. Consequently, it can be seen clearly that the superiority of Xelox for shorter hospital stay with the similar Overall Survival (OS) to mFolfox6.

On this consideration, before this trial, [name] has been conducting an open nonrandomized prospective study comparing laparoscopic surgery with Xelox chemotherapy and open surgery with mFolfox6 chemotherapy for resectable colorectal cancer, and the interim analysis has proved that the former provides faster postoperative recovery and potentially sustained better quality of life throughout treatment [32].

In the view of the separate superiority of the laparoscopy, Fast-track perioperative treatment and Xelox chemotherapy, and the possibility of the integration of these three essential treatments in colorectal cancer, the new notion "Fast Track Multi-Discipline Treatment" (FTMDT) for the integration of these three treatments is promoted in this FTMDT trial. And this FTMDT model is supposed to substantially reduce the length of hospital stays with equal safety and effectiveness, gain the better long-term recovery outcomes, and give patients a better quality of life.

The 2 × 2 balanced factorial design for this randomized prospective controlled FTMDT study tries to answer 2 corresponding questions. The I and II groups versus the III and IV groups is designed to answer the research question "Is Fast-track multidiscipline treatment model safe and effective, compared to conventional treatment?", while the I group versus II group aims to answer "Is laparoscopy an essential component of FTMDT-trial and how important role does it play?"

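### The chemotherapy safety endpoint is limited to treatment-related events in an open trial; counting events of any cause would keep unblinded attribution out of the Xelox versus mFolfox6 comparison

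*Protocol article*

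**What the plan says.** Under Primary and secondary endpoint measures, the second secondary outcome is "Chemotherapy related adverse events according to NCI CTCAE (Common Terminology Criteria for Adverse Events) Version3.0". The abstract uses the same restriction: "The secondary endpoints are the quality of life, chemotherapy related adverse events, surgical complications and hospitalization costs". The only other safety outcome is surgical: "Surgical complications mainly include injury of the ureters, intraoperative transfusion, infection of incision, anastomotic leakage and readmission". The article names no endpoint that counts adverse events of any cause during chemotherapy.

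Under Study design: "This FTMDT-trial is an open randomized prospective and controlled study".

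Safety is part of the first study question: "Is it safe and effective to combine Xelox chemotherapy with laparoscopy and fast-track perioperative treatment". The Discussion assigns the contrast: "The I and II groups versus the III and IV groups is designed to answer the research question" of whether the model is safe and effective. Groups I and II receive Xelox; groups III and IV receive mFolfox6.

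The adjuvant chemotherapy rows of Table 1 give the mFolfox6 groups "Peripherally inserted central catheter and care of PICC in outpatient clinic every week" and state that the Xelox groups have no such catheter.

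**The concern.** CTCAE standardises the name and grade of an event. It does not settle its cause. Read literally, an endpoint of related events therefore needs a second decision for each event, and in an open trial that decision can be made with the regimen known. The Background also records a prior expectation that Xelox is more manageable to tolerate. If the share of events called related differs between regimens, the comparison of I+II with III+IV mixes toxicity with attribution. That can create a difference where none exists or mask a real one.

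Catheter events show the difficulty best. They can arise only in groups III and IV. A line infection or thrombosis can be credited to the chemotherapy programme, because the line is there to deliver it, or to the device. The decision moves the count in one programme only.

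At stake is the chemotherapy part of the safety answer to question 1. If events judged unrelated were never recorded, no later analysis could recover them.

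**Working it through.** The article states no rate, power or sample size for this endpoint, so there is no figure to reproduce. What follows is an illustration.

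**Inputs from the article (Sample size calculation)**
- Enrolment of 340, of whom 64% are expected to need adjuvant chemotherapy: 340 × 0.64 = 217.6, about 218.
- Two programmes of equal size: 218 / 2 = 109 patients each.
- Significance level 5%. The article sets it for hospital stay and does not give sidedness; it is borrowed here as two-sided.

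**Assumed inputs (not in the article)**
- True proportion of patients with a qualifying event, p: 30%, 40% or 50%, the same in both programmes.
- Share called related: 90% under mFolfox6; 80%, 75% or 70% under Xelox.

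**Formulas**
- Observed rates: a = 0.90p (mFolfox6) and b = sp (Xelox), where s is the Xelox share.
- Spurious difference: a − b = p(0.90 − s).
- Standard error: SE = √[(a(1 − a) + b(1 − b)) / 109].
- Probability of a nominally significant result, with z = (a − b)/SE: Φ(z − 1.96) + Φ(−z − 1.96).

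**Worked case.** With p = 40% and s = 75%: a = 0.40 × 0.90 = 0.36 and b = 0.40 × 0.75 = 0.30. SE = √[(0.2304 + 0.2100)/109] = 0.0636, z = 0.06/0.0636 = 0.94, probability 0.157.

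**Creating a difference (true rates equal)**

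| True rate | Shares (mFolfox6/Xelox) | Observed | Spurious difference | P(nominally significant) |
|---|---|---|---|---|
| 30% | 90/80% | 27% v 24% | 3 points | 0.08 |
| 30% | 90/70% | 27% v 21% | 6 points | 0.18 |
| 40% | 90/80% | 36% v 32% | 4 points | 0.10 |
| 40% | 90/75% | 36% v 30% | 6 points | 0.16 |
| 40% | 90/70% | 36% v 28% | 8 points | 0.25 |
| 50% | 90/80% | 45% v 40% | 5 points | 0.12 |
| 50% | 90/70% | 45% v 35% | 10 points | 0.33 |

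With equal shares in both programmes the probability stays near 0.05.

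**Hiding a difference.** Suppose the true rates are 30% under mFolfox6 and 50% under Xelox. With every event counted, the same formula gives power of about 0.87. Shares of 90/80% give observed rates of 27% v 40% and power of about 0.54. Shares of 90/70% give 27% v 35% and about 0.25.

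**Catheter events.** Each mFolfox6 patient whose only event is a catheter event moves that programme's rate by 1/109 = 0.9 points, up if counted and down if not. The direction is therefore not fixed: classing such events as unrelated would favour mFolfox6, opposite to the illustration above.

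**The case against.** The strongest reply is that the article does not say that a causality judgement is made. The phrase may simply mean events in the chemotherapy phase. The outcome list sets chemotherapy events beside surgical complications, and Data collection and monitoring divides the information in the same way. Recording rules and tables of all events are commonly left to the full protocol or analysis plan, and their absence from an article proves nothing. This stands, and it is why the point is conditional on related being used as a filter. It does not remove the point, because the stated endpoint permits that use and a change of wording would rule it out.

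Other parts of the reply also stand:
- Incision infection, anastomotic leakage and readmission are already assigned to surgical complications, so they are poor examples of doubtful attribution.
- Catheter events are a real burden of the mFolfox6 programme. Counting them is not in itself a bias; leaving their inclusion to case-by-case attribution is the weakness.
- Laboratory toxicities leave less room for judgement than symptoms or device events.
- Related events are a conventional chemotherapy endpoint, and the article plans no significance test on this one.

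A reader might infer that the team has declared Xelox the safer regimen in advance. The documents do not go that far. The superiority named in the Discussion concerns hospital stay, and the same section expects the model to have equal safety. Only the remark on tolerability in the Background bears on adverse events. A reader might also infer that unrelated events will go unrecorded; the article does not say so.

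**Conclusion.** The point holds as a modest improvement to a secondary endpoint. The trial is open, and its only stated chemotherapy safety endpoint is limited to related events. If that limit works as a causality filter, knowledge of the regimen can enter the I+II versus III+IV comparison, most plainly through catheter events.

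On the assumed rates the spurious difference is about 3 to 10 percentage points, and the chance of a nominally significant result is about 0.08 to 0.33 instead of 0.05. These figures rest on 109 patients per programme, true event rates of 30-50%, attribution of 90% against 70-80%, and a two-sided 5% test that the article does not plan. They show what is possible; the actual size and direction cannot be found from the article.

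The documents do not support calling this an error or a contradiction in the plan, nor saying that a bias in favour of Xelox will occur. The hospital-stay result is unaffected.

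**What to change.** Base the chemotherapy safety comparison of I+II with III+IV on all adverse events of any cause, graded by CTCAE 3.0. Count them from the first chemotherapy dose to the same fixed interval after the last dose in all four groups, with catheter events included. Report chemotherapy-related events as a secondary breakdown.

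The cost is a change of endpoint wording and, if not already done, recording events whatever their presumed cause. It needs no extra visits or staff. Background events unrelated to treatment will slightly dilute true differences.

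The change removes attribution bias only. Reporting and grading remain unblinded, and contact stays unequal: Table 1 gives Xelox at most 24 hours in hospital every 3 weeks, against 3 days every 2 weeks plus weekly catheter care for mFolfox6. Detection may therefore still differ, and the report should say so.

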### Statistical analysis

#### Sample size calculation

Hospital stay is the primary endpoint. From the evidence in the researches [13,14,22-26], we estimate the hospital stay of laparoscopic and open surgery with Fast-track perioperative treatment is 6 and 8 days. Xelox chemotherapy has at most 1 hospitalization day for each cycle followed by taking Capecitabine orally at home, for a total of 8 cycles. Therefore, we calculate the hospital stay for groups I and II at 14 and 16 days. According to our previous research [27], the hospital stay of laparoscopic and open surgery with conventional perioperative treatment is 12 and 14 days. mFolfox6 chemotherapy requires at least 3 hospitalization days for each cycle, totally 12 cycles. So, we calculate the hospital stay of III and IV group is 48 and 50 days.

With the standard deviation of 6 days of mean hospitalization days, a total sample size of 218 would have a power of > 0.85 to detect a minimum reduction of 2 days in hospital stay among the 4 groups, using a 5% significance level. The III stage or high-risk II stage account for 64% of the total colorectal cancer patients [28], and these patients need the adjuvant chemotherapy according to the NCCN Clinical Practice Guidelines in Oncology-Colon Cancer Guideline 2009 (Version 2.2009) [29]. For this trial we will enroll 340 patients and have 85 patients in each group.

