#### Economic evaluation

As one of the secondary outcomes, we would analyze the balance between the reduction of hospitalization days and the hospitalization cost, and evaluate whether or not FTMDT is a more economical colorectal disease treatment model.

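### The cost endpoint covers hospitalization cost only, but it is used to judge the economy of a treatment model whose comparator includes weekly outpatient catheter care

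*Protocol article*

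**What the plan says.** The section Primary and secondary endpoint measures lists cost as the fourth secondary outcome and defines it in one sentence: "Hospitalization costs are calculated from the first day in hospital to the last day that adjuvant chemotherapy is finished". The abstract also names the endpoint as hospitalization costs.

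Under Economic evaluation the article says "we would analyze the balance between the reduction of hospitalization days and the hospitalization cost", and that the purpose is to "evaluate whether or not FTMDT is a more economical colorectal disease treatment model". The Discussion goes further and expects the model to save cost over the whole course of treatment.

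Table 1 (section Perioperative treatment) describes chemotherapy in the conventional arms as including "Peripherally inserted central catheter and care of PICC in outpatient clinic every week". The corresponding Xelox entry rules out a PICC.

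On where capecitabine is taken, Sample size calculation says that "Xelox chemotherapy has at most 1 hospitalization day for each cycle followed by taking Capecitabine orally at home, for a total of 8 cycles", and the Discussion says that "the Capecitabine intake from 1st to14th day can be done in home". Neither place says where the drug is dispensed or on which bill it appears.

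**The concern.** The measure and the conclusion differ in scope. What is counted is hospitalization cost; what is to be concluded is whether a whole treatment model, from surgery to the end of chemotherapy, is the more economical one. This would matter little if care outside hospital were alike in all groups. It is not. Moving care out of hospital is part of what distinguishes the two packages, and the article itself assigns recurring outpatient care to one side only.

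The main question is answered by comparing groups I+II (all Xelox) with III+IV (all mFolfox6), so the uncounted items line up with the contrast. A hospitalization-only difference then partly reflects where care was delivered and not what it cost in total.

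**Working it through.** **1. The plan's own figures.** Expected stay = surgical stay + cycles × inpatient days per cycle, with all inputs from Sample size calculation.

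- Group I: 6 + 8 × 1 = 14 days
- Group II: 8 + 8 × 1 = 16 days
- Group III: 12 + 12 × 3 = 48 days
- Group IV: 14 + 12 × 3 = 50 days

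All four agree with the article. For a patient having full chemotherapy, the expected saving is 48 − 14 = 50 − 16 = 34 inpatient days. The article gives no cost figure to reproduce.

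**2. Outpatient PICC care left out (groups III and IV).** Table 1 gives 12 cycles at two-week intervals, so 12 × 2 = 24 weeks.

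- Upper bound: one visit per week for 24 weeks = 24 visits. This assumes that the line stays in throughout and that no care falls within an admission.
- Each two-week cycle contains a 3-day admission. If one of the two weekly care episodes falls within it, 24 − 12 = 12 outpatient visits remain.
- Averaged over all randomized patients, with the article's 64% needing chemotherapy and all of them completing it: 0.64 × 24 = 15.4, or 0.64 × 12 = 7.7.

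Leaving these out lowers the recorded cost of the conventional arms and so works against FTMDT.

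**3. Capecitabine possibly left out (groups I and II).** 8 cycles × 14 days = 112 days per patient completing Xelox; averaged as above, 0.64 × 112 = 71.7 days. This is the maximum, and it is zero if the drug is billed to each cycle's admission. Any part left out works in favour of FTMDT.

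**4. Net direction.** Let a PICC visit cost v and an uncounted capecitabine day cost c, both in units of one inpatient day. These are assumed quantities, since the article gives no prices. With 24 visits and all 112 days uncounted, the omitted cost is 24v in the conventional arms and 112c in the Xelox arms. The measure favours FTMDT if c > 24v/112 = 0.21v and works against it if c is smaller. With 12 visits the threshold is 12v/112 = 0.11v.

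**5. What it would take to reverse the conclusion.** If all else costs the same, the full saving under FTMDT is 34 + 24v − 112c. It turns negative when c > (34 + 24v)/112.

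| v | Visits | Threshold for c |
|---|---|---|
| 0 | – | 34/112 = 0.30 |
| 0.25 | 24 | 40/112 = 0.36 |
| 0.5 | 24 | 46/112 = 0.41 |
| 1 | 24 | 58/112 = 0.52 |
| 1 | 12 | 46/112 = 0.41 |

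The table does not show that a reversal occurs. It shows that, if capecitabine is not on the inpatient bill, the endpoint as defined could not detect one.

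**The case against.** The strongest objection concerns capecitabine. Of the two items, only uncounted capecitabine could make FTMDT look falsely economical, and the article does not show that it goes uncounted. Study design says that every chemotherapy cycle is given in hospital and that the insurance system favours this for payment, so the drug may well be handed out and billed at the admission. This stands. A reader might infer that the cost measure is tilted towards FTMDT, or that a finding of lower cost would be wrong. The documents support neither: the only omission they establish works against FTMDT, and if capecitabine is on the inpatient bill, that omission makes the measure conservative for the new model.

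It can also be said that the window is continuous and, for Xelox, may close on a day at home, so that all costs within it might be meant. But the window fixes the period, not the kind of cost, and the abstract, the endpoint definition and the economic section all name hospitalization cost. If all costs were intended, the wording needs correcting anyway.

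A third objection is that an article leaves cost items and perspective to the full protocol. That would answer a complaint about missing detail. Here the article states the scope and also states a conclusion wider than that scope. A hospital perspective is legitimate, provided that the conclusion is labelled accordingly.

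Finally, the reach is limited. Cost is a secondary outcome, and whether laparoscopy repays its extra expense is a comparison of I with II, where both groups receive Xelox. This stands too.

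**Conclusion.** The point holds as a mismatch between a stated measure and a stated conclusion. A hospitalization-only cost leaves out outpatient PICC care that the article assigns to groups III and IV alone: at most about 24 visits per patient completing mFolfox6, about 12 if alternate care coincides with admissions, and about 15 or 8 per randomized patient at 64% on chemotherapy. Patients who stop early would have fewer. An opposite omission of up to 112 capecitabine days per patient completing Xelox depends on billing that the article does not describe.

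Without prices, neither the amount nor the net sign of any bias can be given, and no claim is made that the economic conclusion will be wrong. It simply does not follow from inpatient cost alone. The problem is confined to the I+II versus III+IV cost comparison. It has little bearing on I versus II, and none on the primary endpoint or the sample size.

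**What to change.** Over the window already stated, define the cost endpoint as inpatient bills plus outpatient PICC insertion and care plus capecitabine wherever it is dispensed, and say so in both the endpoint definition and the economic section. This needs an outpatient billing extract or a short cost form for each patient on chemotherapy, which is a small burden.

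If only hospital bills can be obtained, keep the endpoint and narrow the conclusion: report which approach has the lower inpatient hospitalization cost, state whether capecitabine is on those bills, and do not extend the result to the economy of the whole treatment model. This option costs nothing.
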